# Efficacy and safety of YQFM (YiQiFuMai lyophilized injection) on acute ischemic stroke (FAST): rationale and design for a randomized, double-blind, placebo-controlled trial

**DOI:** 10.1186/s12906-025-05036-0

**Published:** 2025-07-22

**Keywords:** Acute ischemic stroke, YiQiFuMai lyophilized injection, Efficacy, Safety, Randomized controlled trial

## Abstract

**Background:**

Low blood pressure at acute ischemic stroke onset is associated with both short- and long-term adverse outcomes. Studies have shown that YQFM (YiQiFuMai lyophilized injection) can ameliorate neurological deficits in ischemic stroke.However, all of these studies are all small-sample clinical observations lacking rigorous study design for AIS with inappropriate blood pressure.

**Aims:**

To describe the design of the YQFM aimed at reducing the disability rate in AIS patients with inappropriate blood pressure.

**Methods:**

This trial is a prospective, multicenter, randomized, double-blind, placebo-controlled, superiority trial aimed at evaluating the efficacy and safety of YQFM in reducing the disability rate in patients with acute hypoperfusion stroke within 90 days. We will recruit 480 patients with AIS within 48 h of symptom onset from 24 hospitals, who have large atherosclerosis, systolic pressure ≤ 155 mmHg, and an NIHSS score of 4–18. Eligible patients will be randomly assigned to receive either YQFM or 0.9% NaCl injection once daily for 10 days and will be followed up until the 90th day after stroke onset.The primary outcome will be the proportion of patients with mRS ≤ 2 at 90 days after patient recruitment. Secondary outcomes will include the proportion of early neurological deterioration at 7 days, patient self-reported outcomes and the syndrome score at 10 days, MMSE scale and BI scale at 90 days.During the trial, adverse events will be recorded. These data will be analyzed according to the predetermined statistical analysis plan.

**Conclusion:**

This study is the first randomized controlled double-blind trial to evaluate the efficacy and safety of YQFM in patients with AIS. This trial will provide evidence-based data for YQFM application in AIS with inappropriate blood pressure.

**Clinical trial registration:**

ChiCTR2300074125 was registered on 31 July, 2023. For more information, please visit Clinical Trials.gov at https://www.chictr.org.cn/showproj.html?Proj=200686.

**Graphical Abstract:**

[figure not shown]

**Supplementary Information:**

The online version contains supplementary material available at 10.1186/s12906-025-05036-0.

## Background

Stroke is a disease characterized by high incidence, high disability and recurrence rates, and frequent complications. Moreover, stroke is the third leading cause of death in the world and the first in China, posing a significant threat to human life [1]. Ischemic encephalopathy affects the quality of life and poses a severe economic burden to patients’ families and society [2–4].

Blood pressure (BP) is often altered in acute stroke [5, 6]. It is well known that extremely high BP is positively associated with adverse clinical outcomes[7, 8]. However, randomized controlled trials on blood pressure lowering have yielded mixed results, hypertensive patients, compared to normotensives, are more likely to have better chances of survival as well as improved cerebral outcomes [9–11]. Previous studies have revealed a “U-shaped” relationship between admission blood pressure and poor outcomes in brain infarction [12–16]. Both low and extremely high blood pressure can lead to poor outcomes [17, 18]. The best prognosis was observed at a systolic blood pressure (SBP) of 160–179 mmHg in the International Stroke Trial (*n* = 17398). In another study, the best prognosis was observed at an SBP of 150–169 mmHg. A SBP between 150 and 200 mmHg represents the values most likely to be associated with surviva [14, 15]. A transition from low to high risk was observed for SBP < 155 mm Hg or for SBP > 220 mm Hg. Patients with SBP < 155 mm Hg were significantly more likely to die within 90 days when compared to those with SBP in the range of 156 to 220 mm Hg [15].

Low SBP in acute ischemic stroke may reduce cerebral perfusion, which may extend the infarction area [19]. Factors like hypotension can cause hemodynamic abnormalities, resulting in insufficient cerebral perfusion pressure, ischemia, and hypoxia of brain tissue. These conditions can lead to neuronal cell death [20–22].

Guidelines from the American Heart Association/American Stroke Association recommend that, for patients with low blood pressure, hypotension and hypovolemia should be corrected to maintain systemic perfusion levels necessary to support organ function. However, no studies have addressed the treatment method of low BP in patients with stroke. Volume expansion therapy has limited effectiveness and increases the burden on the heart, limiting its clinical applications.Clinically, nerve nourishing treatments are often administered, but their effect is not satisfactory [23].

Therefore, it is particularly urgent to explore effective drugs for AIS with inappropriate blood pressure. Alternative or complementary treatment methods have been widely used, and Shengmai preparations have achieved satisfactory therapeutic effects in the treatment of this type of AIS [24, 25]. The use of Shengmai preparations in patients with AIS and low blood pressure has been recommended by the Guideline for the Diagnosis and Treatment of Cerebral Infarction with Integrated Traditional Chinese and Western Medicine (2023).

Currently, the marketed drugs of Shengmai preparations include Shengmai injection and YQFM. YQFM is a lyophilized powder injection, which is convenient for storage and transportation. Therefore, this study selects YQFM as the experimental drug. YQFM [26], a purified extract of Panax ginseng, Ophiopogon japonicus, and Schisandra chinensis, is widely used in the treatment of cardiovascular and cerebrovascular diseases. Research has shown that YQFM can effectively improve the neurological deficit (NFDS) score and daily life index (BI) of patients with acute cerebral infarction [27, 28]. However, these data have been obtained in small-sample clinical observations, and the quality of evidence is relatively low. Therefore, this multicenter, randomized, double-blind, placebo-controlled clinical trial will evaluate the clinical efficacy of YQFM in improving disability in patients with AIS. It aims to obtain high-quality, evidence-based data and improve clinical efficacy in AIS patients with inappropriate blood pressure.

## Methods

### Study design

The FAST trial is a prospective, multicenter, randomized, double-blind, placebo-controlled study. This study will enroll 480 subjects. Eligible patients will be assigned to the YQFM group or placebo injection group at a 1:1 ratio and stratified blocked randomization by the study center.The main purpose of the experiment is to test if YQFM is more effective than a placebo in achieving a favorable functional status, defined as an mRS score ≤ 2 at 90 days in patients with AIS. Figure 1 shows the flow diagram of this experiment. The study protocol was described, and a complete checklist is available according to the Standard Protocol Items: Recommendations for Interventional Trials (SPIRIT) guidelines (see Additional File 2 in Supplementary Material) [29].

**Fig. 1 Fig1:**
[figure not shown]
The flowchart of the FAST trial. *Note: Patients’ blood pressure will be measured between 6 and 9 a.m. using the same model of blood pressure monitor. The average of three blood pressure measurements will be recorded

### Trial population

Patients from 24 hospitals in 14 provinces in China were recruited for the study (Fig. 2). The detailed inclusion and exclusion criteria are listed in Table 1.

Recruitment posters will be posted at these hospitals, so that patients can learn about the study and contact researchers. Participants were screened according to screening criteria and informed of the risks and benefits of participating in the study, as well as the collection of blood samples.If patients agree to participate in the study, they will sign an informed consent form. Recruitment began in November 2023, with initial completion expected in December 2025.If there are very serious cases of toxic side effects or insufficient recruitment, the trial will be stopped.

**Table 1 Tab1:** Inclusion and exclusion criteria

• **Inclusion criteria** • Diagnosed as having acute ischemic stroke; • Large artery atherosclerosis ischemic stroke according to the TOAST classification; • Patients with acute ischemic stroke within 48 h of onset; • Patients aged 18–80 years; • Patients with NIHSS score of 4–18 points; • An average Systolic blood pressure at least 3 times ≤ 155 mmHg before the patient’s enrollment; • Being informed about the study and signing informed consent.	• **Exclusion criteria** • Patients who have received intravenous thrombolysis or intravascular treatment; • Posterior circulation infarction; • Stroke caused by tumors; • Previous history of stroke and mRS ≥ 2 points before the onset of this stroke; • NIHSS 1a > 2 points; • Patients with a yellow and greasy tongue layer; • Patients with other diseases that limit the evaluation of neurological function or affect patient follow-up; • Patients with severe abnormal liver and kidney function with serum ALT, AST, or SCr over two times the upper limit of the reference range; • Have another serious life-threatening illness with life expectancy of less than 3 months; • Pregnant, with recent family planning, or lactating women; • Currently participating in other interventional clinical trials.

**Fig. 2 Fig2:**
[figure not shown]
Geographic distribution of participating sites across mainland China

### Randomization and blinding method

Four hundred and eighty eligible patients with acute ischemic stroke will be randomized to treatment and control groups in a 1:1 ratio using a central randomized approach by investigators within 48 h of symptom onset. Figure 3 shows the flowchart of the included subjects in this study. An independent third-party “Independent Data Committee” will be responsible for the design of randomization schemes and the management of randomization systems.The method of stratified blocked randomization will be utilized to generate a random number grouping table using the professional statistical software PROC PLAN. A random allocation scheme will then be created, with a block size set to 4. It is required that there be 2 treatment groups and 2 control groups in the scheme.

The packaging, weight, and size of the two groups of drugs should be consistent. The allocation sequence and drug coding will be generated by an independent third-party “Independent Data Committee”. The process of drug coding configuration will be recorded in writing and confirmed by the corresponding participants. The researcher of this study will enroll patients strictly based on the order of random allocation table numbers. Researchers will implement randomization by using an online randomization system. They will log into the EDC system to apply for patient randomization codes and drug codes. Afterward, they will submit the requested drug code to the medication administrator.

The researcher and research assistant responsible for enrolling patients, collecting patient clinical information, and assessing outcomes, as well as participants and care providers, are blinded during the research process. Specialized personnel from each unit will be responsible for drug preparation. Dark brown infusion bags and infusion sets will be used for drug infusion to ensure the same appearance of drugs in the two groups.The recovery of relevant infusion supplies and remaining drugs will also be the responsibility of a dedicated person. Throughout the study, the researcher responsible for drug use will record the usage of the investigational drug but will not participate in the collection of other information from the subjects or exchange drug grouping information with others.

**Fig. 3 Fig3:**
[figure not shown]
The schematic diagram of the patient timeline

### Management and preservation of blind bottoms

The random allocation scheme, selected block length, and random initial seed parameters will be used as blind bases. These blind bases will be configured in the EDC system and stored by the project responsible unit and blinding unit.

### Requirements for unblinding and emergency unblinding

Two levels of unblinding will be employed in this study, with the first level being performed before the statistical analysis and division of the different groups. After the statistical analysis is completed, secondary unblinding will be performed to identify the experimental and control groups. If serious adverse events (SAEs) occur in the clinical trial, and emergency unblinding is required, the main researcher (project leader) will decide whether to proceed with emergency unblinding.

### Subject withdrawal

Subjects were screened and found to be ineligible based on the enrollment criteria.Subjects were not provided experimental medication after enrollment.There were no data after randomization.During the experiment, the subjects were found to be unfit to continue the experiment. Consequently, the investigator decided to withdraw the cases from the experiment.Subjects refused medication and assessment, and as a result, they were lost to follow-up.

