### Interventions

Patients eligible for the study will be assigned to one of the different groups and will receive one of the following two treatments:

A 5.2 g YQFM injection is diluted into 250 mL of 0.9% sodium chloride injection and administered intravenously once daily for 10 days.The placebo injection, which is a 10 mL 0.9% sodium chloride injection, is diluted into 250 mL 0.9% sodium chloride injection and administered through intravenous drip once daily for 10 days.

All enrolled patients will receive guideline-directed medical therapy in accordance with the Chinese guidelines for the diagnosis and treatment of acute ischemic stroke in 2018 [30]. The treatment measures mainly include lipid-lowering, blood sugar-lowering, and antiplatelet aggregation therapies, and it is required that each hospital maintains the same drug varieties when using medications with similar efficacy.On this basis, the test group received YiQiFuMai lyophilized injection and the control group received 0.9% sodium chloride injection for 10 days. The treatment assignment is illustrated in Fig. 1.

Administration of other TCM or Chinese patent medicines, similar in function and indications with the investigational medicine, and of all traditional Chinese medicine injections will be prohibited during the treatment period. Moreover, during the study period, the use of Chinese herbal decoctions (granules) and other traditional Chinese patent medicines for the treatment of acute ischemic stroke will be prohibited.

If an SAE occurs, a participant or their legally authorized representative requests withdrawal from the study, or a participant does not comply with the prescribed intervention, the investigational drug will be discontinued. Any reasons for discontinuing the intervention will be recorded.

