### Monitoring and quality control

Before enrolling the subjects, on-site centralized training, video training, and other forms of training will be conducted for the researchers in each sub-center included in the implementation plan. Each sub-center will issue a researcher folder, which will be saved by a designated person.

A unique login ID will be used by the clinical research coordinator to collect information at each visit point and record data in a timely, accurate, complete, and clear manner in an electronic case report form (eCRF), which will be signed by the researcher. All medical center researchers will make reasonable efforts to follow up patients throughout the entire study period.

A third-party professional monitoring agency will undertake the monitoring tasks of our research group. This agency will regularly monitor all study data and conduct quality control of the study data. Additionally, a clinical research associate will regularly monitor the research data and researcher folder through both online monitoring using an Electronic Data Acquisition System and on-site monitoring.

In this study, inspectors were selected from personnel not directly involved in the experiment. They formulated the inspection process and completed the on-site inspection. At the beginning, middle, and end of the experiment, one third of the research centers were inspected respectively. The inspection focused on the group leader unit, the unit with the fastest and most enrolled subjects, the unit with the first cooperation, and the unit with abnormal data.At the end of the trial, all study centers were inspected at least once.

A third party statistical agency will complete the statistical analysis of the data. Researchers, statistical analysts, monitors, and data managers will design a data verification plan. The data administrator will draft a data audit report and lock the database, which will be carried out jointly by the research team leader and statistical analysts.

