### Management of adverse events and adverse reactions

We will record any AEs that occur during the course of the study and will assess whether they are related to the investigational drug, properly handled, and tracked until they are resolved, or until the condition stabilizes. AEs and unexpected events will be reported in a timely manner to the Data Security and Monitoring Board, Ethics Committee, and Chief Investigator.

If AEs occur during the trial, the investigator may take necessary treatment measures according to the condition to ensure the safety of the subjects, record them, and decide whether the subjects’ participation should be terminated in the trial. In case of serious adverse events, the subjects should be withdrawn from the clinical trial, and appropriate measures for the subjects should be taken immediately. The insurance for the enrolled subjects will be covered by this study, ensuring the protection of their rights.

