### Data analysis

The missing data are processed by multiple interpolation. If the primary efficacy index is missing, the previous result is carried forward according to the intentionality analysis.If there is a valid value carried forward after randomization, the last observation is used for carry-over.

The main efficacy measure (the percentage of patients with mRS ≤ 2 ) will be compared and analyzed using the chi-squared test. The statistician will perform covariate adjusted analyses and covariate unadjusted analyses. Subgroup analyses will include sex, age, systolic blood pressure, and the baseline NIHSS score.

For dichotomous outcomes, such as the percentage of BI ≥ 90, distribution of mRS scores, proportion of early neurological deterioration, and recurrence rate of stroke, we will use the chi-squared test or Fisher’s exact test to compare the distribution of patients between the two groups.Logistic regression is utilized to estimate the 95% CI. For continuous variables, including neurological function scores, MMSE scores, PRO scale, cerebral blood flow, such as changes from baseline to treatment endpoints, Student’s t-test or Wilcoxon rank-sum test is employed to analyze the differences between the two groups.Survival data will be estimated using the Kaplan-Meier method, survival curves will be plotted, and efficacy will be evaluated using log-rank tests.

According to the safety set data, statisticians compare and analyze the differences in the incidence of adverse events, major adverse events, and liver and kidney dysfunction, as well as routine blood and urine tests between the two groups. For most safety data, Cox proportional-hazards models are used to estimate the hazard ratios between the two treatment groups.

When 50% of the subjects have completed the study, an interim analysis will be conducted. The continuation or suspension of the study is determined according to the analysis results. If the analysis results indicate that valid results cannot be obtained, the study will be terminated immediately. The study will continue if data analysis suggests that efficacy may be achieved at the end of the study.

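### The withdrawal list does not separate stopping study drug from leaving the trial, so the D90 mRS of undosed or investigator-withdrawn randomised patients may never be collected

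*Protocol article*

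**What the plan says.** The Subject withdrawal section of the protocol article gives five grounds without separating them by stage or by consequence:

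- failed eligibility: "Subjects were screened and found to be ineligible based on the enrollment criteria";
- no study drug: "Subjects were not provided experimental medication after enrollment";
- no data: "There were no data after randomization";
- found unfit while the trial is running: "Consequently, the investigator decided to withdraw the cases from the experiment";
- refusal of medication and assessment, leading to loss to follow-up.

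Other sections touch the same patients:

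- **Interventions** deals with stopping treatment separately. After an SAE, a request to withdraw or non-compliance, "the investigational drug will be discontinued".
- **Management of adverse events and adverse reactions** goes further for one of those events: "In case of serious adverse events, the subjects should be withdrawn from the clinical trial".
- **Monitoring and quality control** says researchers will "make reasonable efforts to follow up patients throughout the entire study period".
- **Data analysis** names multiple imputation for missing data. For a missing primary outcome, "the previous result is carried forward according to the intentionality analysis", on condition that a valid value exists after randomisation.
- **Appendix C** schedules mRS at screening, Day 1, Day 30 and Day 90 only.

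**The concern.** The primary outcome is the proportion with mRS of 2 or less at D90. An intention-to-treat comparison needs that score, or a defensible substitute, for every randomised patient, whether or not study drug was given or continued.

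Two grounds in the list work against this. An undosed patient and a patient judged unfit can both be followed to D90, yet the article classes both as withdrawn, and the second explicitly leaves the experiment and not just the drug. No criterion for unfitness is given, so investigator judgement decides. Patients who deteriorate before the first infusion, or who are thought unfit to go on, are plausibly those with a poorer prognosis, so the missing scores are unlikely to be missing at random.

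This is a rule of conduct, not an analysis detail. An analysis plan can define who is in the primary set, but it cannot recover a D90 score that was never taken.

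**Working it through.** **Does the list reach randomised patients?** Under Randomization and blinding method, the randomisation code and the drug code are requested together. A patient for whom study drug was available but not given has therefore normally been allocated already. The no-data ground mentions randomisation in terms, and the unfit ground applies while the trial is running. The eligibility ground is tied to screening and is set aside here.

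**What is left to analyse?** Set Appendix C beside Data analysis:

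| Withdrawn, with no further visits | Latest mRS available | Usable for carry-forward? |
|---|---|---|
| Before D30 | Day 1 | Only if the Day 1 score was taken after randomisation, which the chart does not say; acute-phase in any case |
| Between D30 and D90 | D30 | Yes |

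The treatment phase is 10 days, so undosed patients and most patients found unfit during treatment fall in the first row.

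**Size.** The plan gives no withdrawal rate by ground, so there is no figure of its own to reproduce. Inputs from Sample size calculations are control success 65%, YQFM success 76.5% (planned difference 76.5 − 65 = 11.5 points), 240 per arm and 20% dropout (0.20 × 240 = 48 per arm). My assumptions are no true effect (65% in both arms), a fraction w withdrawn from one arm only, and a fraction s of those who would have reached mRS of 2 or less.

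*Case A: withdrawn patients are deleted.* Shift = (0.65 − s·w)/(1 − w) − 0.65.

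- w = 2%, s = 0: 0.65/0.98 − 0.65 = +1.3 points
- w = 5%, s = 0: 0.65/0.95 − 0.65 = +3.4 points (3.4/11.5 = 30% of the planned difference)
- w = 10%, s = 0: 0.65/0.90 − 0.65 = +7.2 points
- w = 5%, s = 30%: 0.635/0.95 − 0.65 = +1.8 points. With 228 against 240 patients, the two-sided rejection rate at nominal 5% is about 7%.

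*Case B: a Day 1 mRS above 2 is carried forward, so each withdrawn patient counts as a failure.* Shift = −s·w.

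- w = 5%, s = 0: 0 points
- w = 5%, s = 30%: −0.05 × 0.30 = −1.5 points

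The same 5% withdrawal thus moves the arm by anything from −1.5 to +3.4 points, depending on handling and on who was withdrawn.

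**Cost of keeping everyone.** Suppose 5% of the YQFM arm are undosed or withdrawn and respond at the control rate (assumed). That arm's rate becomes 0.95 × 76.5% + 0.05 × 65% = 75.9%, and the difference falls from 11.5 to 10.9 points. With 240 per arm (pooled-variance test, two-sided 0.05), power falls from 79.3% to 74.8%.

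**The case against.** The case on the other side has four parts, and much of it stands.

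1. **Ineligibility.** A reader might infer that randomised patients later found ineligible are removed. The text says they were screened and found ineligible, which most naturally means screen failure, and Appendix C places the eligibility check and TOAST at screening. The documents do not support the stronger reading. The item needs a label, no more.
2. **Exclusion from analysis.** A reader might infer that withdrawn patients are dropped and that the intention-to-treat comparison is broken. The article nowhere says so. Carry-forward and imputation only make sense if some patients without a D90 score stay in. Intention to treat is also mentioned only once, within the missing-data rule, and the analysis sets may be defined in a document not shown.
3. **Inflated effect.** A reader might infer that the arm losing more patients gains. That follows only under deletion. Under carry-forward of a poor Day 1 score the shift is zero or negative.
4. **Loss from one arm only.** Enrolling and assessing staff are blinded and allocation is central. An undosed patient has not been exposed to either treatment, so there is no evident route by which that loss depends on arm. The unfit ground could follow treatment effects, but that decision is also meant to be blinded. One-sided loss is a stress case.

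None of this restores the missing score. The promise of reasonable efforts at follow-up is general and is not reconciled with a rule that takes the case out of the experiment.

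**Conclusion.** The concern holds in a limited form. For randomised patients who are undosed or judged unfit, the article's withdrawal rule ends participation, and no section keeps their D90 mRS. Because mRS is not scheduled between Day 1 and D30, the carry-forward rule then has at most an acute-phase value to work with, and possibly none that qualifies. That undermines the intention-to-treat handling of the primary outcome; it does not show that the comparison is broken.

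No single bias figure can be attached. The range of −1.5 to +3.4 points at 5% withdrawal rests on assumed rates, assumed outcomes and loss from one arm only. What can be said is that the primary result would depend on who was withdrawn and how the gap was filled, and the article fixes neither. The SAE wording raises the same difficulty: one section stops the drug while another withdraws the patient from the trial, and the SAEs listed under Safety outcomes include progressive stroke, which bears on the primary outcome.

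**What to change.** Rewrite Subject withdrawal so that it:

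- labels ineligibility found before randomisation as screen failure;
- separates stopping study drug from leaving follow-up;
- states that D30 and D90 mRS are sought for every randomised patient, including those undosed, found ineligible after randomisation or withdrawn by the investigator, unless consent to follow-up is withdrawn;
- states that all randomised patients are analysed in the allocated arm.

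Then reconcile Interventions, Monitoring and quality control, Management of adverse events and adverse reactions, and Data analysis with that text, including how a D90 score that is still missing is handled. Which events stop the drug is for the sponsor to reconcile and need not change for this purpose.

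The cost is protocol wording and a reminder to sites, since the D30 and D90 visits are already in the schedule. The statistical price is slight dilution by undosed or ineligible patients: about 0.6 points of the planned 11.5 in the 5% example above. Trial population gives recruitment from November 2023 with initial completion expected in December 2025, and each D90 window that passes without a score cannot be recovered, so the change should be made promptly.
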